### Sample size

A maximum of 150 participants will be recruited for the study. Power analysis for the primary outcome measure indicates that 98 participants are needed for a medium effect size. We anticipate that some participants will be lost to follow-up, lose their tablets or incur damage to them, thus the data that we obtain at the end of the trial is likely to come from fewer than the 150 registered participants.

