#### Randomization

After screening, participants are randomized to either the active or wait-list control group using block randomization (four per block).

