### Assessments

Baseline questionnaires will consist of items relating to demographics, help-seeking, psychological distress, depression, suicidality and impulsivity (Table 1). Measures will also be administered immediately after participants complete the interventions, and at 6 weeks follow-up. The Patient Health Questionnaire 9 (PHQ-9) is the depression scale of the Patient Health Questionnaire, and consists of nine items, each scoring from 0 (not at all) to 3 (nearly every day). Participants are asked to rate how problematic the items have been for them over the previous fortnight. Overall scores range from 0 to 27 with 0 to 4 representing no or minimal depression, 5 to 9 representing mild depression, 10 to 14 moderate depression, 15 to 19 moderately severe depression, and 20 to 27 severe depression [18].

**Table 1 T1:** Overview of measures

**Variable**	**Test measure**	**Screener**	**Brief assessment**	**Baseline**	**Within app**	**Post-test**	**Follow-up**
Screener, part 1	Questions	X					
Psychological distress	K10	X		X		X	X
Depression	PHQ-9	X	X	X		X	X
Suicide intent	5 questions	X					
Demographics	Questions			X			
Mental health service utilization	Client Service Receipt Inventory			X			
Impulsivity	BIS-11			X		X	X
Suicidal ideation	DSI-SS			X		X	X
Suicidal ideation and plan	2 questions				X		

BIS-11, Barratt Impulsivity Scale; DSI-SS, Depressive Symptom Inventory – Suicidality Subscale; K10, Kessler Psychological Distress Scale; PHQ-9, Patient Health Questionnaire 9*.*

The Kessler Psychological Distress Scale (K10) contains ten items rated on their occurrence over the previous 4 weeks from 1 (none of the time) to 5 (all of the time). Total scores range from 10 to 50 with psychological distress being categorized as follows: those scoring 1 to 20 are likely to be well; those scoring 20 to 24 are likely to have a mild mental disorder; those scoring 25 to 29 are likely to have a moderately severe mental disorder; those scoring 30 and above are likely to have a severe mental disorder [17]. The scale has been used across several populations [19] and is a valid and reliable instrument sensitive to the detection of mental health conditions within the population [20].

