### Statistical analyses

To test the hypothesis that the self-help intervention is superior to the control condition, the analysis will be conducted on an intention-to-treat basis following the pertinent BMJ & Consort guidelines. Missing observations at follow-up will be imputed by regression imputation or multiple imputations, stratified for predictors of outcome and loss to follow-up. Relative improvements in frequency and intensity of suicidal thoughts for the experimental group in comparison with the control group will be calculated using Cohen’s *d*. For this confirmatory analysis the primary outcome measure is used (the DSI-SS). For the analyses of the secondary outcome measures, a Bonferroni correction will be applied to control the overall Type I error rate.

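### The confirmatory DSI-SS analysis is described only as a Cohen's d: no test or model is named, and the role of the baseline DSI-SS is not stated

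*Protocol article*

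**What the plan says.** The Statistical analyses section of the protocol article opens with a testing purpose: "To test the hypothesis that the self-help intervention is superior to the control condition, the analysis will be conducted on an intention-to-treat basis". The between-group quantity it then gives is this: "Relative improvements in frequency and intensity of suicidal thoughts for the experimental group in comparison with the control group will be calculated using" Cohen's d. The next sentence attaches the confirmatory label and the outcome to it: "For this confirmatory analysis the primary outcome measure is used (the DSI-SS"). For the rest, "For the analyses of the secondary outcome measures, a Bonferroni correction will be applied to control the overall Type I error rate". No test, model, interval or significance level is named for the primary outcome.

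The baseline value will be available. Table 1 marks the DSI-SS at baseline, post-test and follow-up, and the Assessments section says: "Measures will also be administered immediately after participants complete the interventions, and at 6 weeks follow-up".

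The Sample size section states: "Power analysis for the primary outcome measure indicates that 98 participants are needed for a medium effect size". It also sets a ceiling: "A maximum of 150 participants will be recruited for the study". The Abstract splits these 75 and 75.

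**The concern.** The purpose and the method do not match. Cohen's d is a standardised difference. It carries no decision rule, so computing it neither supports nor rejects superiority. A d can also be formed from raw post-test means, from mean changes or from baseline-adjusted means, so the label does not say which comparison will be made. The reference to improvements leans towards change from baseline, but does not settle it.

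Two things are at stake. One is that the choice between a post-only, a change-score and an adjusted comparison stays open until the data are in, for the very analysis called confirmatory. The other is precision. The first two comparisons are less efficient than adjusting for a baseline score that is collected anyway, and the article itself expects losses to follow-up and warns of high attrition.

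**Working it through.** **Inputs from the article.** Two arms with equal allocation (75 and 75, Abstract). 98 needed for a medium effect and a maximum of 150 (Sample size). DSI-SS at baseline, post-test and follow-up (Table 1).

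**Assumptions, none stated in the article.** Medium effect read as d = 0.5 in units of the outcome SD; two-sided alpha 0.05; power 80%; equal SD at baseline and outcome; baseline-outcome correlation r shown from 0.3 to 0.7.

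**Step 1: the plan's own figure.** For an unadjusted comparison the normal approximation gives a total N = 4(1.960 + 0.842)²/d² = 4 × 7.85/0.25 = 125.6, so 126. The noncentral t gives 128. Neither is 98. Other routes come closer:
- ANCOVA, two-sided, r = 0.5: 98.
- Repeated-measures ANOVA, between-group factor, two measurements, correlation 0.5, f = 0.25: 98.
- Unadjusted one-sided test: 100 (normal) or 102 (t).

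Several routes reach 98 or nearly so, and the article does not say which was used. The figure can therefore be neither confirmed nor refuted.

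**Step 2: variance of each comparison, relative to post-only.**
- Post-only: 1.
- Change score: 2(1 − r), which is 1.4, 1.0 and 0.6 at r = 0.3, 0.5 and 0.7.
- ANCOVA: 1 − r², which is 0.91, 0.75 and 0.51.

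The change score exceeds ANCOVA by 2(1 − r) − (1 − r²) = (1 − r)², and post-only exceeds it by r². For r between 0 and 1 both gaps are positive, so adjustment costs nothing but one degree of freedom.

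**Step 3: total N and power.** N scales with the variance factor. The values below are from the noncentral t, with one further degree of freedom spent for ANCOVA.

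| r | N for 80%: ANCOVA | N: change | N: post-only | Power at 98: ANCOVA | Change | Post-only |
|---|---|---|---|---|---|---|
| 0.3 | 118 | 178 | 128 | 73% | 54% | 69% |
| 0.5 | 98 | 128 | 128 | 81% | 69% | 69% |
| 0.7 | 68 | 78 | 128 | 93% | 89% | 69% |

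At r = 0.6 change scores need 104 and have 78% power at 98, so they reach 80% at 98 only when r is a little above 0.6.

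**Step 4: at full recruitment.** With all 150 analysed, an unadjusted two-sided test has about 86% power. Its requirement of 128 tolerates a loss of (150 − 128)/150 = 14.7%.

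**The case against.** The strongest reply is that this is a condensed article. Models and covariates are commonly left to an analysis plan, which is not shown here, and preferring ANCOVA to an unstated model would be a matter of taste. The paragraph can also be read with the confirmatory analysis being the superiority test in its opening sentence, and d merely the reporting metric.

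Part of this stands. A reader might infer that the trial has no test of its hypothesis. The text does not support that: the section says superiority will be tested, applies Bonferroni to the secondary outcomes, and follows a power analysis, all of which presuppose significance tests. What is true is that no test is named. A reader might also infer that baseline will be ignored. That rests on silence, since nothing excludes a covariate and the talk of improvement suggests that baseline is used in some way. Finally, a reader might infer that the described analysis cannot support 98. That is not established. The inputs behind 98 are missing, a one-sided unadjusted test needs 100 to 102, and change scores suffice if r is high enough. If 98 did come from a calculation that uses baseline, that would suggest the trial team meant to use it.

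What does not stand is the defence that this is only missing detail. The section does choose a procedure and places the word confirmatory directly on it, and that procedure cannot decide the question. An analysis plan would have to add to or depart from the published sentence to repair it.

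**Conclusion.** The point holds as a mismatch between purpose and method. Superiority is to be tested, and the one thing described for the DSI-SS is an effect size whose underlying comparison is left open. The article should be corrected on this, but the finding does not show that the trial is underpowered or that its sample size is wrong.

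The cost of leaving it depends on which comparison would be used and on r. With 98 analysed, adjustment is worth 12 percentage points of power over either alternative at r = 0.5 (81% against 69%). Against change scores it is worth 19 points at r = 0.3 (73% against 54%) and 4 points at r = 0.7 (93% against 89%). With nearer 150 analysed, the unadjusted test is already adequate for d = 0.5, and the gain is mainly a narrower interval. All these figures rest on the assumed d, alpha, power and r. That adjustment is at least as precise, apart from one degree of freedom, does not depend on those choices.

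**What to change.** Replace the sentence on Cohen's d with a named test: a two-sided 5% ANCOVA of the DSI-SS with baseline DSI-SS as covariate, or an equivalent baseline-adjusted mixed model. Report the adjusted mean difference in DSI-SS points with its 95% CI, and keep Cohen's d as a descriptive addition. Analyse PHQ-9, K10 and BIS-11 in the same way, each with its own baseline, and leave the planned Bonferroni correction in place for them. Beside the 98, state the effect size, alpha, sidedness, power, test and assumed correlation, so that it can be checked against the named analysis.

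The cost is wording only. Table 1 already collects all four scales at baseline, so no new data are needed. The article gives the trial as still recruiting; the change should be recorded before outcomes are compared by arm.

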## Discussion

This paper describes the study protocol for a pilot randomized controlled trial of an app for suicide prevention in young Indigenous people. To our knowledge, this is the first trial of a mobile-based app for suicide prevention, and the first randomized controlled trial of suicide prevention with Indigenous Australians. Despite fears that focusing on suicidal ideation might give rise to further suicidal thoughts and even attempts, there is no evidence to validate this idea [15,28].

Several limitations apply to the study protocol of this self-help app. First, online interventions tend to have a high attrition rate. Dropout from the study can introduce a selection bias and therefore be a threat to validity. To minimize this, participants will be asked for additional contact details so that even if the intervention is not completed, follow-up assessments may still be collected. Further, each participant will be contacted via email or text message three weeks into the intervention or wait-list period for a brief assessment. A reminder to continue with the app will be provided at this point.

A further limitation is that none of the measures provides a psychiatric diagnosis. The intent is to keep the measures to a minimum in order to increase retention, as the research participants may find too many measures a barrier to participation. Some participants are also likely to have low literacy skills. Long, complex measures would be a significant problem for these participants. To overcome literacy problems, participants have the option of face-to-face or telephone assistance to complete the measures. Moreover, the app targets suicidal ideation irrespective of diagnosis and, as such, a measure of suicidality is a more appropriate primary outcome measure.

Researching suicide prevention is difficult; perhaps even more so within Indigenous communities. Because of this, little is known about what works with this population. While suicide rates have dropped amongst the general population over the last two decades, they remain stubbornly high in the Indigenous community [29]. This study will make a significant and unique contribution to our knowledge about suicide prevention and treating suicidal ideation.

## Trial status

Currently recruiting.

## Abbreviations

BIS-11: Barratt Impulsivity Scale; DSI-SS: Depressive Symptom Inventory – Suicidality Subscale; K10: Kessler Psychological Distress Scale; PHQ-9: Patient Health Questionnaire 9.
